### Measurements

#### Baseline measurements

Patients will complete the Dutch VISA-P (Victorian Institute of Sport Assessment) questionnaire at baseline [10,11]. The VISA-P questionnaire is designed to measure severity of patellar tendinopathy. The VISA-P score is the primary outcome variable. Patients will also complete a baseline questionnaire that asks for demographics, sports participation and medical history, knee injuries and previous treatment. Anthropometrics of the participants are also collected. Pain experienced during ADL and sports will be rated on a VAS. Finally, pain during one and during 10 decline squats on a 25° decline board is rated on a VAS.

#### Follow-up measurements

At all follow-up moments (before treatments 2 and 3 and 1, 4, 7 and 12 weeks after treatment) the VISA-P questionnaire is completed. At the 7-week and 12-week follow-up pain VAS score during ADL, sports and functional tests (decline squat) are also collected. At these two moments patients answer a question about subjective improvement and their overall satisfaction with the treatment. A follow-up of 12 weeks was chosen because Peers et al. showed favourable effects of a similar protocol within a 12-week period [6]. Adverse reactions and side effects will also be recorded during the follow-up period.

#### Web-based diary

Every week the patients will record their sports activities, pain during and after these activities, and concurrent medical treatment in a web-based diary.

### Sample size

Sample size is calculated based on the VISA-P score 12 weeks after treatment. A baseline score of 64 points is expected in symptomatic subjects with an SD of 19 points, based on previous investigations [18]. A difference in the VISA-P score of 15 points at the end of the study (12 weeks) is considered to be clinically relevant. With a power of 80% and an alpha of 5%, 28 tendons per group are needed to detect a difference of 15 points between treatments on the VISA-P questionnaire. Since Peers [6] reported no drop-out of patients because of pain (during or after treatment) in a similar protocol, we do not expect a higher-than-normal drop-out rate.

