### Statistical analyses

Results will be analysed using SPSS version 16 (SPSS, Chicago) according to the intention-to-treat principle. Descriptive statistics will be used to describe the characteristics of the focused and the radial shockwave group and the outcome variables at the evaluation moments. The difference on outcome variables between treatment groups after 12 weeks will be assessed using t-tests. A repeated-measures analysis will be used to determine whether there is a difference on outcome variables between the two groups over time. Analyses will be performed for the primary and secondary variables. A p-value < 0.05 is considered statistically significant.

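### The stated 80% power at 28 tendons per group holds only if no more than about 6.5% of 12-week scores are lost, and the plan allows for no loss

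*Protocol article*

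**What the plan says.** The Sample size section of the protocol article bases the calculation on the VISA-P score 12 weeks after treatment. It takes its spread from baseline data ("A baseline score of 64 points is expected in symptomatic subjects with an SD of 19 points") and treats a 15-point difference as clinically relevant. The result is: "With a power of 80% and an alpha of 5%, 28 tendons per group are needed".

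Drop-out gets one sentence. It notes that an earlier study with a similar protocol lost no patients because of pain, and concludes "we do not expect a higher-than-normal drop-out rate". The section gives no attrition rate, no inflated number and no separate recruitment target.

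The Statistical analyses section plans intention-to-treat analysis and sets the primary comparison: "The difference on outcome variables between treatment groups after 12 weeks will be assessed using t-tests". It also plans a repeated-measures analysis over time, but the sizing refers to the single 12-week score.

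**The concern.** A rate that is not higher than normal is still a rate, and the section makes no provision for it. The evidence offered covers one cause of loss, pain during or after treatment. It does not address patients who move away, stop responding or fail to return the last questionnaire. The 12-week score falls about 14 weeks after baseline, because the third weekly session comes two weeks after the first.

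The 12-week t-test uses only the scores that are present at that visit. Intention to treat fixes the group in which a patient is analysed; it does not supply a missing score. If 28 per group is also the number enrolled, every missing 12-week score comes out of a small margin.

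This affects how a non-significant result is read. The Discussion section presumes neither therapy to be better, so such a result is a real possibility, and its weight depends on the power actually reached.

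**Working it through.** **Inputs from the plan.** Difference 15 points, SD 19 points, alpha 5%, power 80%, equal groups (Sample size section); two-sample t-test at 12 weeks (Statistical analyses section). Sidedness is not stated, and I take it as two-sided. A one-sided 5% test would need only 20 (normal approximation) or 21 (t-test) per group, which does not fit 28. Observations are treated as independent.

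**Step 1: reproduce the plan's figure.**

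Normal approximation: n = 2 × (1.96 + 0.8416)² × (19/15)² = 25.19, so 26 per group.

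Noncentral t with 2n − 2 degrees of freedom and noncentrality 15 / (19 × √(2/n)):

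| Evaluable per group | Power |
|---|---|
| 24 | 76.3% |
| 25 | 78.1% |
| 26 | 79.7% |
| 27 | 81.2% |
| 28 | 82.7% |

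The t-test requirement is 27. The stated 28 is reproduced with one tendon per group to spare (two by the normal approximation).

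**Step 2: the loss at which power reaches 80%.** By the t-test, power is exactly 80% at n = 26.18, so the tolerable loss is 1 − 26.18/28 = 6.5%. By the normal approximation it is 1 − 25.19/28 = 10.0%. In whole tendons, losing one per group leaves 81.2% and losing two leaves 79.7%.

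**Step 3: power if enrolment stops at 28.** The article gives no attrition rate, so 5% to 20% is an assumed range.

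| Assumed loss | Evaluable per group, 28 × (1 − loss) | Power, t-test | Power, normal approximation |
|---|---|---|---|
| 0% | 28 | 82.7% | 84.0% |
| 5% | 26.6 | 80.6% | 82.1% |
| 10% | 25.2 | 78.4% | 80.0% |
| 15% | 23.8 | 76.0% | 77.7% |
| 20% | 22.4 | 73.3% | 75.2% |

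**Step 4: the same comparison adjusted for baseline VISA-P.** With correlation r between the baseline and 12-week scores, the residual SD is 19 × √(1 − r²). At 25 evaluable per group (3/28 = 10.7% loss) the noncentrality is 15 / (residual SD × √(2/25)), with 2 × 25 − 3 = 47 degrees of freedom. The article gives no r, so I show a range.

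| Assumed r | Residual SD | Noncentrality | Power at 25 per group |
|---|---|---|---|
| 0.2 | 18.62 | 2.85 | 79.7% |
| 0.3 | 18.12 | 2.93 | 81.7% |
| 0.4 | 17.41 | 3.05 | 84.7% |
| 0.5 | 16.45 | 3.22 | 88.4% |

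The unadjusted t-test at 25 per group has 78.1%.

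**The case against.** The strongest reply is that nothing is miscalculated. The plan's inputs give 26 or 27, so 28 is reproduced and already carries a small cushion. Any shortfall needs a loss rate that the article does not give. At 5% loss power is still 80.6%. At 10% it is 78.4% by the t-test and 80.0% by the normal approximation, a difference of little practical weight. All of this stands.

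A second reply is that the drop-out sentence claims only that drop-out will not exceed the usual level. Evidence on pain is relevant to that, because both treatments are given without anaesthesia at a fixed intensity. This also stands. The sentence does not claim zero attrition; its weakness is that the usual level is neither quantified nor provided for.

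A third reply is that the article states how many tendons are needed, not how many will be enrolled, and a recruitment target may be in the full protocol. This too is fair. A reader might infer that the planned enrolment fails to deliver 80% power, or that ordinary attrition necessarily takes it below 80%. The document supports neither: it gives no enrolment figure separate from 28, and its own inputs keep power above 80% up to about 6.5% loss.

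The list of threats should also stay narrow. Under intention to treat, another treatment or a new injury is not in itself a missing score. A missed interim questionnaire does not reduce the number analysed at 12 weeks.

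**Conclusion.** The point holds in conditional form. The 28 per group is arithmetically sound as a number of evaluable tendons, with 82.7% power. The 80% statement survives only up to about 6.5% loss of 12-week scores by the planned t-test (about 10% by the normal approximation). The section implies ordinary drop-out, makes no allowance for it, and supports its remark with evidence on one cause only.

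If enrolment stops at 28, the shortfall is under 2 points at 10% loss and becomes clear at 15% to 20% (76.0% to 73.3%). This rests on a two-sided test, the stated SD of 19 also applying at 12 weeks, and an assumed loss rate. It is a modest weakness, not an error in the sample size.

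The most useful part is the remedy. Baseline VISA-P is already collected, and adjusting for it recovers power at no cost in patients. The gain depends on an unknown correlation, and the entry limit of a VISA-P score below 80 narrows the baseline range and may lower it. At r = 0.2 and 25 per group the gain over 78.1% is small and power stays just under 80%; from r = 0.3 upward power exceeds 80%.

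**What to change.** 1. In the Sample size section, say that 28 per group is the number of evaluable tendons at 12 weeks and that 80% power holds only up to about 6% to 7% loss. Do not rest the drop-out statement on pain-related drop-out alone.
2. In the Statistical analyses section, make the 12-week VISA-P comparison an analysis of covariance with baseline VISA-P as covariate, in place of the unadjusted t-test. If its power is quoted, give it as a range over assumed correlations, such as the 79.7% to 88.4% above, and not as a single figure.

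The cost is one sentence in the first section and a change of the primary test in the second, which should be fixed before outcome data are examined. It needs no added patients, visits or measurements. Adjustment restores precision only; it does not remove bias if the patients who are lost differ from those who stay.

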### Statistical analyses

Results will be analysed using SPSS version 16 (SPSS, Chicago) according to the intention-to-treat principle. Descriptive statistics will be used to describe the characteristics of the focused and the radial shockwave group and the outcome variables at the evaluation moments. The difference on outcome variables between treatment groups after 12 weeks will be assessed using t-tests. A repeated-measures analysis will be used to determine whether there is a difference on outcome variables between the two groups over time. Analyses will be performed for the primary and secondary variables. A p-value < 0.05 is considered statistically significant.

## Discussion

A number of studies have been conducted on the effect of shockwave therapy for patellar tendinopathy. A review of the literature concluded that ESWT seems to be a safe and promising treatment for PT [5]. All included studies except one used focused shockwave therapy.

Radial shockwave generators generate waves that are very different from those generated by focused shockwave generators. Radial shockwaves lack the characteristic features of shockwaves such as a short rise-time, a high peak pressure and non-linearity [7]. Another difference is that radial shockwaves have a more superficial effect on tissue, compared to focused shockwaves which reach a maximal energy in the focus that is located deeper into the tissue [19]. Since the exact working mechanism of shockwave therapy is not well understood, this difference does not imply that radial shockwave therapy is less effective than focused shockwave therapy [20,21]. Each therapy may even have a different working mechanism [22].

It is not known whether there is a difference in effectiveness between these therapies as treatment for PT. Therefore, the aim is of this study is to directly compare the effects of focused shockwave therapy and radial shockwave therapy on patellar tendinopathy in a blinded randomised controlled trial.

## Conclusions

The TOPSHOCK study is the first blinded randomised controlled trial that directly compares focused shockwave therapy and radial shockwave therapy in combination with eccentric decline squat training for the treatment of patellar tendinopathy.

## List of abbreviations used

TOPSHOCK: Tendinopathy Of Patella SHOCKwave; ESWT: Extracorporeal Shockwave Therapy; VISA-P: Victorian Institute of Sport Assessment - patella
